### Ethics

The research project and all related materials were submitted and approved by the appropriate university ethics committees in Bogota (letter reference no. 552 on December 1st 2015) and Bucaramanga (letter reference no. 075 on March 28th 2016).

### Planned analysis

#### Study 1: Cultural adaptation (cultural sensitivity and ecological validity)

Descriptive statistics will report on the results from the quantitative questions on CRQ. The CRQ data collected from the five open questions and the open questions per module will be analysed qualitatively [66]. The feedback will be categorised based on Helms [46] functional, conceptual and linguistic equivalence. The information will be assigned a colour code indicating positive and negative comments and suggestions for improving the programme. Likewise, new categories that might arise from the data will be considered. Finally, the results gathered from experts and users will be incorporated into the *Space from Depression* programme.

#### Study 2: Efficacy trial

All analyses will be based on the intention-to-treat principle. Participants’ data will be included irrespective of treatment compliance. All of the data will be prepared and reviewed in SPSS.

Descriptive statistics will be used to analyse sociodemographic variables (e.g., gender and age). Chi-squared and t-tests will be used to examine demographic differences and clinical characteristics in the groups [67].

Effects will be tested at the 0.05 level. To assess significant changes over time, repeated measures ANOVAs will be performed for the primary outcome measure for depression (PHQ-9) and secondary outcome (GAD-7) [68]. The magnitude of effects within and between the two groups will be established by Cohen’s *d* statistic [67]. This will determine what is considered a small effect (*d* ≥ 0.2), a medium effect (*d* ≥ 0.5) and a large effect (*d* ≥ 0.8) [69].

Analyses will be carried out with participants who have clinically significant changes at the end of the intervention and at follow-up. The assessments will be made using pre-treatment scores, and these will be compared to post-treatment scores and follow-up scores on the outcome measures PHQ-9 and GAD-7. The analysis will be based on the Jacobson & Truax method, where a reliable change equals the difference pre-test and post-test, divided by the standard error of the difference [70].

Linear Mixed Model will be used for repeated measures (PHQ-9, GAD7) on each participant over time; it allows for a variety of correlation patterns (variance and covariance structures) to be explicitly modelled [71]. Also, it allows the measures on each subject to be used while accounting for missing data.

Participants’ responses in the HAT, identifying helpful and non-helpful events in the therapy and their impacts will be analysed qualitatively [66]. At the beginning, individual units of text will be analysed and identified out of their context. Next, these meaning units will be organised into helpful and non-helpful events and their impacts. Finally, these will be grouped into categories, which will be suitably named and defined.

Descriptive analysis will be used to analyse quantitative data from the SAT and their qualitative responses analysed using thematic analysis.

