## Method

### Aims and hypothesis

We aim to assess the efficacy of a culturally adapted cognitive behavioural internet-delivered treatment for college students with depressive symptoms in Colombia. In line with other studies in high-income countries (HICs), and using an already established intervention, we hypothesise that the culturally adapted *Space from Depression* programme will be efficacious, with significant changes within the treatment group and differences post-treatment between the active treatment and the waiting list control group.

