### Sample size

Power analysis, carried out in G-Power using significance level α = 0.05 and power = 0.80 determined 45 subjects would be required for each test condition (active group and waiting list) to observe a moderate effect (*d* = 0.50) post-treatment between groups [54].

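### The PHQ-9 test is described as one of change over time and no between-arm test is named, although the trial is sized on a post-treatment difference between arms

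*Protocol article*

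**What the plan says.** The Protocol article's section on aims and hypothesis predicts efficacy in two parts: "with significant changes within the treatment group and differences post-treatment between the active treatment and the waiting list control group". The sample size section rests on the second part alone: 45 per arm, "to observe a moderate effect (*d* = 0.50) post-treatment between groups".

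The planned analysis for Study 2 then says of the primary outcome: "To assess significant changes over time, repeated measures ANOVAs will be performed for the primary outcome measure for depression (PHQ-9". The same applies to GAD-7. The second model is introduced in similar terms: "Linear Mixed Model will be used for repeated measures (PHQ-9, GAD7) on each participant over time". Neither model is given a group term, a group-by-visit term or a contrast at a named visit. The reliable-change analysis also compares scores before and after treatment.

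The arms are compared on outcome in one sentence: "The magnitude of effects within and between the two groups will be established by Cohen’s *d* statistic". The only tests said to compare the groups concern their characteristics: "Chi-squared and t-tests will be used to examine demographic differences and clinical characteristics in the groups".

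**The concern.** Randomisation supports one inference, the comparison of the arms. The waiting list is untreated only up to week 7, so that comparison is clean at week 7. The text attaches its 0.05 test to a different quantity, change over visits, and gives the arm comparison a size label with neither a test nor an interval.

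The distinction matters here because scores are likely to fall in both arms. Table 1 admits only students with a PHQ-9 of 10 to 19, so some regression to the mean is to be expected whatever the programme does. A test of change over time cannot separate that from a treatment effect.

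If the section is followed literally, the trial could report a significant PHQ-9 result that says nothing about whether the programme beat waiting. If it is followed loosely, the analyst chooses after the fact which output of the model counts as the efficacy result.

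**Working it through.** **1. Does any named test match the sized comparison?**

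| Analysis of PHQ-9 in the plan | Stated target | Tests the arms at week 7? |
|---|---|---|
| Repeated measures ANOVA | change over time | not stated |
| Linear mixed model | repeated measures over time | not stated |
| Reliable change | before versus after, per participant | no |
| Cohen's d | size, within and between groups | right comparison, but no test or interval |
| Chi-squared and t-tests | demographic and clinical characteristics | not named for outcome |

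**2. How often does a time effect reject when the arms do not differ?** The document gives no figure for this, so the inputs are part document and part assumption.

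- From the document: 45 per arm (sample size section), test level 0.05 (planned analysis).
- Assumed: equal SDs at baseline and week 7, set to 1; pre-post correlation ρ of 0.3, 0.5 or 0.7; the same mean improvement δ (in SDs) in both arms, so the true arm difference is zero.

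Let D be the change score, with variance 2(1 − ρ).

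- Time effect, pooled over 90 participants: noncentrality = δ√90 / √(2(1 − ρ)).
- Group-by-time with two visits: difference in mean D between arms, divided by √(2s²/45), where s² is the pooled variance of D. Its expectation is zero for every δ.

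By hand for δ = 0.3, with critical value about 1.987:

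- ρ = 0.3: 0.3 × 9.487 / 1.183 = 2.41; rejection about Φ(0.42) = 66%.
- ρ = 0.5: 0.3 × 9.487 / 1.000 = 2.85; about Φ(0.86) = 80%.
- ρ = 0.7: 0.3 × 9.487 / 0.775 = 3.67; about Φ(1.69) = 95%.

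Simulation of 20,000 trials per setting agrees (entries are for ρ = 0.3 / 0.5 / 0.7):

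| Shared improvement | Time effect | Change in active arm alone | Group-by-time |
|---|---|---|---|
| 0.2 SD | 35% / 47% / 68% | 20% / 26% / 40% | 5.0% / 4.7% / 4.9% |
| 0.3 SD | 66% / 80% / 95% | 38% / 51% / 72% | 5.1% / 4.9% / 5.2% |
| 0.5 SD | 98% / 99.6% / 100% | 79% / 90% / 99% | 5.1% / 4.7% / 5.2% |

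With no shared improvement, all three tests reject in about 5% of trials.

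**3. Would an overall test over all visits do instead?** The wait list section starts that arm's treatment after week 7. The assessments section places follow-up at week 20, that is 20 − 7 = 13 weeks after the post-treatment visit. The programme lasts seven weeks, so a waiting-list participant who starts on time is due to finish at 7 + 7 = 14 weeks. An overall group or group-by-time test over baseline, week 7 and week 20 therefore mixes the randomised comparison with data in which both arms have been offered treatment. The week-7 contrast has to be named.

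**4. What this does not use.** The calculation takes 45 per arm as stated. From the stated inputs, 2 × (1.960 + 0.842)² / 0.50² gives 63 per arm two-sided (64 with the t distribution), so 45 does not reproduce for a plain two-sample comparison. That is a separate matter, and nothing above depends on it.

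**The case against.** The case on the other side has four parts.

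- **The article condenses a fuller plan.** Model terms and contrasts are commonly left to an analysis plan, which is not shown. A two-arm repeated measures ANOVA ordinarily includes a group-by-time term, and the mixed model can carry one. This stands: a reader might infer that the trial has no between-arm test, and the document does not support that. But the text does more than stay silent. It states a purpose for the test, and that purpose is not the comparison on which the trial was sized.
- **Change over time is part of the hypothesis.** This also stands. A reader might infer that the plan tests something nobody hypothesised; that is wrong, because change within the treatment group is hypothesised. Still, a time effect pooled over both arms does not isolate that change, and the randomised part is left without a named test.
- **The neighbouring sentences speak of effects within and between groups.** Read generously, the 0.05 level could cover between-group effects, with Cohen's d giving their size. That is possible but not what is written. Equally, the 0.2, 0.5 and 0.8 cut-offs are descriptive labels, and it would be unfair to treat them as decision rules.
- **The rejection rates rest on assumptions.** True: neither the shared improvement nor the correlation is in the document, and a small shared improvement would often go undetected. The rates also do harm only if a time effect is presented as efficacy, and no sentence says that it will be.

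**Conclusion.** The point holds as a mismatch between the stated purpose of the PHQ-9 test and the comparison for which the trial was randomised and sized. The section names no between-arm test of PHQ-9, while the sample size rests wholly on the post-treatment arm difference and the hypothesis rests on it in part.

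The possible size is large but conditional. If both arms improve by 0.3 SD and the correlation lies between 0.3 and 0.7, a time effect would be significant in roughly two thirds to nearly all trials of a programme with no effect, against about 5% for group-by-time. At 0.2 SD the range is 35% to 68%. These figures illustrate how such a test behaves; they do not predict this trial's error rate. The part that needs no assumption is that a time effect cannot show efficacy against a waiting list, whatever its p-value.

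This should be corrected. It does not show that the authors intend to claim efficacy from a time effect, or that their models lack the right term.

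**What to change.** In the planned analysis for Study 2, replace the stated purpose of the PHQ-9 test with wording such as:

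> Efficacy is tested by the difference between arms in PHQ-9 at week 7, estimated from the linear mixed model as the group-by-visit contrast at week 7 and accounting for baseline PHQ-9, two-sided at the 0.05 level and reported with its 95% confidence interval. The same contrast for GAD-7 is secondary. The between-group Cohen's d is given with a 95% confidence interval. Effects of time and changes within groups, including those at week 20, are descriptive and are not evidence of efficacy.

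Two-sided is a choice to be made explicit, since the document states 0.05 without saying which. Naming week 7 keeps data collected after the waiting list starts treatment out of the efficacy test. If a full analysis plan already contains this contrast, the article's sentence only needs to be brought into line with it. Recruitment had begun when the article was written, so the change should be dated and made before outcomes are examined by arm.

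The change needs no new data, visits or software. The one small downside is that a significant time effect can no longer be presented as an efficacy result.

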#### Assessments

In study 1 cultural sensitivity will be determined through the ‘*top-down*’ revisions performed by the clinician researcher [name], together with translation and customisation. Ecological validity using experts and users will assess the cultural relevance of the *Space from Depression* (*Yo puedo sentirme bien*) programme using the Cultural Relevance Questionnaire (CRQ).

In study 2, the efficacy trial, participants will be assessed at baseline, post treatment, and at 3-month follow-up. Details of the measures are described in Table 3.

**Table 3 Tab3:** Study measures to be used

Study	Measure	Assessed variable	Time of assessment
Study 1 cultural validity	Cultural Relevance Questionnaire (CRQ)	Culturally adapted internet-delivered treatment	Completed by experts and users before the trial.
Study 2 efficacy trial	Patient Health Questionnaire (PHQ-9)	Depression symptoms	Baseline, post-treatment and follow- up
	Generalised Anxiety Disorder 7 (GAD-7).	Anxiety symptoms	Baseline, post-treatment and follow- up
	Sociodemographic & Clinical History Questionnaire	Gender, age, marital status, education, occupation, socioeconomic status and clinical history	Baseline
	Helpful and Hindering Aspects of Treatment (HAT)	Helpful and hindering aspects of treatment	After each session
	Satisfaction with Treatment (SAT)	Satisfaction with therapy	Post-treatment

Participants will be assessed at baseline through the Patient Health Questionnaire (PHQ-9), Sociodemographic & Clinical History Questionnaire and Generalised Anxiety Disorder-7 (GAD-7). At the beginning of each session participants will be asked to reflect on their previous session and complete the Helpful Aspects of Treatment Form (HAT). PHQ-9 and GAD-7 will be completed at week 7 and at follow-up (week 20 / 3 months). In addition, satisfaction with Treatment (SAT) will be administered at week 7.

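### Two inferential tests of the primary outcome PHQ-9 are planned at the 0.05 level, a repeated-measures ANOVA and a linear mixed model, and neither is named as primary

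*Protocol article*

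**What the plan says.** All of this is in the protocol article, mainly under Planned analysis, Study 2: Efficacy trial.

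- Analysis principle: "All analyses will be based on the intention-to-treat principle". The next sentence explains this as meaning that "data will be included irrespective of treatment compliance". It concerns adherence and does not mention missed assessments.
- Software: "All of the data will be prepared and reviewed in SPSS".
- Significance level: "Effects will be tested at the 0.05 level". No split between tests is given.
- First method: "repeated measures ANOVAs will be performed for the primary outcome measure for depression (PHQ-9) and secondary outcome (GAD-7". Its stated purpose is to assess change over time. The visits that enter it and the handling of missing values are not stated.
- Second method, after a paragraph on clinically significant change: "Linear Mixed Model will be used for repeated measures (PHQ-9, GAD7) on each participant over time". One reason given is that "it allows the measures on each subject to be used while accounting for missing data".
- Visits, under Assessments: "participants will be assessed at baseline, post treatment, and at 3-month follow-up".

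Aims and hypothesis has two parts: change within the treatment group, and a post-treatment difference between arms. Sample size rests on the between-group difference after treatment alone (d = 0.50, 45 per arm). Procedure foresees participants who do not complete the measures and plans e-mails and telephone calls to them.

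**The concern.** Two methods are assigned to one primary outcome at the same significance level. Neither is called primary, confirmatory, supportive or sensitivity. If they disagree, the article does not say which one answers the efficacy question, and an analyst who has seen both could choose. This goes beyond detail left to an analysis plan: the article itself names both methods and gives them equal standing.

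The two methods also use different participants when data are incomplete. A repeated-measures ANOVA in its ordinary form needs a value at every visit it includes, so anyone missing one of them drops out of the analysis entirely. A mixed model keeps every participant's available measurements. Only the mixed model is credited with handling missing data, and no imputation is mentioned for the ANOVA. Run that way, the ANOVA would be an analysis of completers under an intention-to-treat statement that covers all analyses. At stake are the type I error of the primary conclusion, the number of participants behind it, and possibly bias if those who leave differ between arms.

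**Working it through.** The article gives no figure for this point to reproduce. The 45 per arm is taken as given; whether it follows from its stated inputs is a separate question.

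**Inputs from the article.** 45 per arm (90 in total), three visits, alpha 0.05, d = 0.50.

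**Assumptions, not in the article.** SD 1 at each visit, correlation 0.5 between visits, an ANOVA on all three visits tested by its group-by-time interaction, and the drop-out rates and mechanisms below. The mixed model is represented by a baseline-adjusted week-7 comparison of everyone seen at week 7. Results are from simulations of at least 4,000 replicates. At a true 5% the Monte Carlo standard error is at most √(0.05 × 0.95 / 4000) = 0.0034, or about 0.3 percentage points.

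**1. Participants kept by the ANOVA, loss at week 20 only.** Kept = 90 × (1 − loss). At 20%: 90 × 0.80 = 72. At 35%: 90 × 0.65 = 58.5, about 59. All 90 still have a week-7 score.

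**2. Two tests with no ranking.** For two valid 5% tests, the chance of at least one false positive is at least 0.05 and at most 0.05 + 0.05 = 0.10. Simulated with no true effect:

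- no loss: 8.9%
- random loss of 20% at week 7 and a further 10% of the rest at follow-up: 8.2%
- 30% and 20%: 8.6%
- 40% and 20%: 9.3%

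This cost does not need informative drop-out.

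**3. Bias and type I error of the ANOVA, no true effect, loss at week 20 only.** Loss follows logit P(loss) = a + b × (week-7 score in SD), with a set to give the overall rate. Bias is in the baseline-to-week-7 contrast between arms among completers, and favours treatment where it is not zero.

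| Mechanism | Loss | Bias (SD) | Type I error |
|---|---|---|---|
| Random in both arms (b = 0) | 20%, 35% | 0 | about 5% |
| Same informative loss in both arms (b = 1) | 20%, 35% | 0 | about 5% |
| Active arm only, b = 0.5 | 20%, 35% | 0.05 to 0.08 | about 6% |
| Active arm only, b = 1 | 20% | about 0.09 | 6 to 7% |
| Active arm only, b = 1 | 35% | about 0.15 | 8 to 9% |

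In the last two rows, counting success on either test gives about 10 to 12%. The test on all week-7 data stays unbiased at about 5% throughout, because week 7 is fully observed in this scenario.

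**4. Power at d = 0.50, random loss.**

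| Missing at week 7, then of the rest at follow-up | Kept by ANOVA | ANOVA | Available-data test |
|---|---|---|---|
| none | 90 | 69% | 77% |
| 20%, 10% | 90 × 0.8 × 0.9 = 64.8 | 53% | 66% |
| 40%, 20% | 90 × 0.6 × 0.8 = 43.2 | 36% | 54% |

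The gap is already 77 − 69 = 8 points with complete data, because the two tests address different contrasts. Only the widening to 66 − 53 = 13 and 54 − 36 = 18 points reflects missing data.

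**5. Limit of the remedy.** If week-7 scores are themselves lost in the active arm through the same mechanism (b = 1, 35%), the baseline-adjusted analysis of observed week-7 data has bias of about 0.22 SD and type I error of about 16%. A mixed model removes bias only from loss that the observed data explain.

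**The case against.** Several stronger readings are tempting, and the article does not support them.

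- **That the ANOVA contradicts the intention-to-treat rule outright.** The text never says that the ANOVA is restricted to complete cases, SPSS is named only for preparing and reviewing the data, and the intention-to-treat sentence is explained through compliance. The tension comes from how the method works when no imputation is stated. Specified imputation would remove it, and such detail may sit in a document not shown. The conditional form stands.
- **That the ANOVA tests the wrong thing because it concerns change over time.** The hypothesis includes change within the treatment group, and a group-by-time test also bears on the difference between arms. Only the sample size is purely between-group.
- **That anyone missing week 20 is lost.** The visits entering the ANOVA are not given. An ANOVA of baseline and week 7 would fit the between-arm hypothesis, since the wait-list arm starts treatment after week 7, and would lose nobody for a missed follow-up.
- **That the ANOVA will show a benefit where none exists.** The bias appears only when loss is related to response differently in the two arms. With random loss, or the same informative loss in both arms, it is zero.

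The either-test figure also depends on the two methods testing different contrasts. If both tested the same contrast on complete data, their p-values would be closer and the inflation smaller. The article fixes the contrast of neither, so this does not settle the matter.

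It is also fair to say that the plan already contains a suitable model and lacks only a sentence ranking the two. That limits the cost of the correction. It does not supply the ranking.

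**Conclusion.** The point holds in this form: two inferential tests of PHQ-9 at 0.05 with no stated primary, one of which, as ordinarily run and with no imputation stated, sits badly with an intention-to-treat statement covering all analyses.

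The missing ranking is established by the text alone. The sizes are illustrations. Under the stated assumptions, accepting either test raises type I error from 5% to about 8 to 9% under random loss, and to about 12% at most in the settings examined. For a three-visit ANOVA taken alone, the range runs from no bias and 5% to about 0.15 SD and 9%, and the upper end needs response-related loss in the active arm only. A reader might infer that the ANOVA is certain to favour treatment, or that the mixed model guarantees an unbiased answer. Neither follows. The article gives no drop-out rate or mechanism, and the mixed model is no cure if week-7 scores are themselves missing informatively.

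Trial status says recruitment began in August 2016 and the study is in progress, so the ranking should be fixed before outcomes are analysed.

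**What to change.** In Planned analysis, Study 2:

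1. Name the linear mixed model, on all randomised participants, as the single primary analysis of PHQ-9. Its primary contrast is the arm difference at week 7, tested two-sided at 0.05. This is the comparison on which the trial is sized, and the last one before the wait-list arm is offered treatment.
2. Use the same model for GAD-7 as the secondary analysis.
3. Label the repeated-measures ANOVA as a supportive completers analysis and state which visits enter it, or drop it.
4. State that the hypothesised within-group change is supportive.

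Because the mixed model relies on loss being explained by observed data, a sensitivity analysis for missing week-7 scores would be a sensible companion.

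The cost is a few sentences. The mixed model is already planned, and no new data, visits or participants are needed.
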